## Abstract

Background: This methodological paper presents both a scientific rationale and a methodological approach for investigating the effects of resveratrol supplementation on mood and cognitive performance in postmenopausal women. Postmenopausal women have an increased risk of cognitive decline and dementia, which may be at least partly due to loss of beneficial effects of estrogen on the cerebrovasculature. We hypothesise that resveratrol, a phytoestrogen, may counteract this risk by enhancing cerebrovascular function and improving regional blood flow in response to cognitive demands. A clinical trial was designed to test this hypothesis. Method: Healthy postmenopausal women were recruited to participate in a randomised, double-blind, placebo-controlled (parallel comparison) dietary intervention trial to evaluate the effects of resveratrol supplementation (75 mg twice daily) on cognition, cerebrovascular responsiveness to cognitive tasks and overall well-being. They performed the following tests at baseline and after 14 weeks of supplementation: Rey Auditory Verbal Learning Test, Cambridge Semantic Memory Battery, the Double Span and the Trail Making Task. Cerebrovascular function was assessed simultaneously by monitoring blood flow velocity in the middle cerebral arteries using transcranial Doppler ultrasound. Conclusion: This trial provides a model approach to demonstrate that, by optimising circulatory function in the brain, resveratrol and other vasoactive nutrients may enhance mood and cognition and ameliorate the risk of developing dementia in postmenopausal women and other at-risk populations.

## 1. Introduction

Dementia disproportionately affects older women (47% by the age of 85 years, compared with 31% of men). It not only destroys cognitive capabilities but also deprives individuals of their independence and places emotional and financial burdens on families, caregivers and society at large. Dementia is predicted to be the top health crisis in this century, outpacing heart disease and cancer in terms of years lost due to disability and there is currently no cure nor means of slowing its progression [1]. Furthermore, there tends to be a substantial gap between the noticeable symptoms of cognitive decline and when medical advice is sought, and a further delay before dementia is diagnosed. In Australia, it takes an average of three years from presentation of first symptoms to diagnosis [2]. As such, quality of life in the later years is likely to be sub-optimal due to impaired cognition. Cognitive impairment may also contribute to decline in physical functioning, such as activities of daily living, and is associated with increased risk of falls in the elderly [3]. Early intervention to maintain high-level cognitive function and well-being may help prolong independent living in older adults. Therefore, it is important to identify feasible lifestyle strategies to counteract cognitive decline in ageing women.

### 1.1. Estrogen, Menopause and Dementia

While women enjoy longer life expectancy, this may not be the only reason for the higher risk of dementia in elderly women. Growing evidence has shown that loss of estrogen after menopause may lead to accelerated deficits in brain function, which may lead to higher risk of dementia [4]. Ageing and many lifestyle diseases are closely related to poor blood circulatory function, including poor perfusion of brain regions. Estrogen targets blood vessels to promote blood flow in the heart, skeletal muscle and particularly in the brain to support cognitive and affective functions. Estrogen binding to estrogen receptors (ER) activates endothelial nitric oxide synthase (eNOS), modulating nitric oxide (NO)-mediated vasodilatation to meet tissue perfusion demands for optimal functioning. Importantly, ER-β are abundantly expressed in the hippocampus, a brain region which subserves learning, memory and neurodevelopmental processes [5], while ER-α are predominantly located in the basal forebrain, which coordinates information processing and attentional function [5]. Therefore deprivation of estrogen at menopause may contribute to the cognitive decline associated with neurological ageing in both executive and memory functions [4]. Executive function governs high-level cognitive functions such as time sharing, sequencing, response inhibition and perseverance, which is crucial for independent living in older adults. In the context of independent living, executive and memory functions are necessary for daily activities such as meal planning, paying bills, keeping medical appointments and ambulation [5]. It is important to acknowledge that resveratrol may also act through SIRT-1 and other mechanisms to increase NO bioavailability and boost cerebral vasodilator responses to cognitive demands [6]. However, little attention has been given to the phytoestrogenic nature of resveratrol and its potential to benefit postmenopausal women as a specific target population.

Epidemiological evidence indicates that hormone replacement therapy (HRT) halves the risk of Alzheimer’s disease in postmenopausal women [7]. However, since publication of the Women’s Health Initiative Study [8] the effects of HRT have been controversial. Five years of HRT use in late postmenopause (>70 years old) resulted in increased risk of breast cancer, stroke, heart disease and dementia, prompting many women to cease treatment and/or look for alternative treatment for their menopausal symptoms. Since the publication of these disturbing findings, there has been no follow-up investigation on whether cessation of HRT could lead to reduced risks. On the other hand, clinical evidence has shown that estrogen administration can augment mood and cognitive function postmenopausally, if commenced during early (peri) menopause rather than late menopause, due to the profound effects of estrogen in the brain [9]. Progressive impairment of cerebrovascular function is implicated in the pathogenesis of dementia [10]. Cerebrovascular responsiveness (CVR) to hypercapnic provocation (a method of assessing endothelial health in the brain) is maintained in women on HRT but is halved in non-HRT users [11]. Likewise, women with lower estrogen levels have poorer cerebral perfusion, which is further compromised during a hot flush episode [12]. HRT users exhibit higher hippocampal and temporal blood flow [measured by single positron emission tomography), which correlates with better performance on memory tasks [13], suggesting that estrogen plays a critical role in neurovascular and cognitive integrity. Impaired cerebral perfusion and executive function also contribute to poor physical function, mood disorders and higher fall rates in older adults [14]. CVR to hypercapnia was positively associated with gait speed and inversely related to number of falls in the elderly [15]. Older adults with slow gait (<0.67 m/s) had poorer CVR while performing the N-back task (a test of executive function) and had poorer test scores on executive function tasks, compared to those with faster gait [16]. Thus more attention needs to be given to the relationships between the neurovascular integrity and cognitive and physical impairments. Taken together, the available evidence strongly supports the hypothesis that cognitive, mood and physical deficits in older women may be attributed to impaired vascular function in the cerebral circulation. Thus maintenance of cerebrovascular function as part of healthy ageing may prevent the burden of cognitive and physical disability in later life. Whether cognitive and physical function deficits in postmenopausal women can be attenuated by improvement of cerebrovascular function is unknown.

### 1.2. How Could Resveratrol Benefit Postmenopausal Women?

Naturally occurring phytoestrogens such as those present in soy and red clover offer a potentially safer alternative to HRT for postmenopausal health. Genistein from soy has been shown to improve NO-mediated systemic vasodilator function in postmenopausal women [17] and thus may have the potential to enhance cerebral perfusion which may in turn improve cognition and mood. Chronic soy isoflavone supplementation has been shown to improve menopausally-related mood, memory, sleep quality and vasomotor symptoms [18]. Moreover, it has also been shown to enhance spatial working memory in young men (with low estrogen levels) [19]. However, its mechanisms of action are still unknown and conflicting evidence has discouraged clinicians from recommending soy isoflavones to menopausal women. Importantly, a large proportion of people lack the enzyme to convert daidzein to equol, which (like genistein) mimics the action of estrogen on ER-β [20], which could explain the variability in outcomes of soy interventions. In a recent study, administering 30 mg of pure (synthetic) genistein significantly reduced hot flushes [21]. Considering that cerebral perfusion is compromised during a hot flush episode [8], the improvement in menopausal symptoms may be partly attributable to enhanced cerebrovascular function. However, this hypothesis has yet to be evaluated.

Resveratrol is a phytoestrogen found in grapes, berries and nuts with multiple targeted benefits including cardiovascular and neurological, particularly attenuating learning impairment and hippocampal degeneration [22]. It may act similarly to estrogen and genistein to confer neurovascular protection by up-regulating eNOS activity, resulting in enhanced NO bioavailability and vasorelaxation [23]. Resveratrol also rapidly stimulates the mitogen-activated protein kinase signalling pathway via both ER-α and ER-β to increase eNOS activity in human endothelial cells at nanomolar concentrations that can be achieved through habitual diet, e.g., a glass of grape juice [24]. Furthermore, resveratrol can also reduce vascular tone via an endothelium-independent mechanism [23]. Given that resveratrol is structurally similar to and mimics the activity of 17-β-estradiol, it may enhance cognition by stimulating ERs [25] to increase perfusion via increased NO production. In human trials, we and others have independently demonstrated its ability to improve endothelial vasodilator function [26,27], cerebral perfusion and memory functions in older adults [28]. We found that 6-weeks daily supplementation with resveratrol (75 mg/day) resulted in a sustained improvement in flow-mediated dilatation in the brachial artery in obese but otherwise healthy older adults. There was also a non-statistical trend towards improvement in performance to the Stroop Test, suggesting that perhaps a longer duration intervention might be needed to see enhancement in cognitive function [26]. A recent study found that daily supplementation (200 mg of resveratrol with 320 mg quercetin) for 6 months in older adults resulted in greater hippocampal activity at rest, assessed by MRI, and retention of words learnt [28]. Whilst improvements in resting state activity may reflect enhancement in the integrity and functionality of the hippocampus, this augmentation does not reveal whether resveratrol can improve the efficiency of cerebral perfusion during cognitively demanding tasks, nor has it been linked to enhanced cognitive performance, mood or physical function. Thus the potential for resveratrol to maintain optimal cognitive health in postmenopausal women who are not taking HRT must now be evaluated.

The primary aim of this study is to see whether daily supplementation with resveratrol for 14 weeks can improve cognition in postmenopausal women in whom age-related endothelial dysfunction is exacerbated by estrogen deprivation. The secondary aim is to see whether improvements in cognition, mood, physical function and aspects of well-being including sleep quality, quality of life, menopausal symptoms and pain are accompanied by improvements in CVR to hypercapnia and/or to cognitive demands.

## 2. Materials and Methods

### 2.1. Study Design

A randomised, double-blind, placebo-controlled (parallel comparison) dietary intervention trial of 14 weeks duration was designed to evaluate the effects of resveratrol supplementation (75 mg twice daily) on cognitive abilities, CVR and overall well-being. The dose was based on data from an acute dose response trial in those with type 2 diabetes mellitus (manuscript in preparation), in which 75 mg resveratrol elicited maximal CVR to hypercapnia when compared with 150 mg and 300 mg doses. Assessments will be made at baseline (week 0) and at the end of the 14-week intervention phase (week 14). The trial will be conducted at the Clinical Nutrition Research Centre, University of Newcastle, in New South Wales, Australia in accordance with the Declaration of Helsinki and Principles of Good Clinical Practice as outlined by the International Conference on Harmonisation. The protocol has been approved by the University of Newcastle’s Human Research Ethics Committee (H-2015-0002; approved on 13 March 2015) and registered with the Australia and New Zealand Clinical Trials Registry on 27 March 2015 (ACTRN12615000291583).

### 2.2. Study Population

Healthy postmenopausal women from the general public residing in the Hunter region of New South Wales were invited to participate following expressions of interest to approved newspaper and radio campaigns. Each volunteer was first provided with an information statement outlining the study objectives and procedures. A health and lifestyle questionnaire that collected information pertaining to their menopausal status, medication and dietary supplement use and current perception of their cognitive status was completed by interested parties. Upon returning the questionnaire, a study investigator pre-screened volunteers via telephone to determine their potential suitability, as described in Table 1, and to invite them in for a screening/baseline visit at the research centre. They were also encouraged to consult with their medical practitioner regarding their intention to participate in this intervention prior to their first visit. Written informed consent was obtained at start of the screening/baseline visit.

Our power calculations (G*Power) [29] showed that 74 participants would give 80% chance of detecting a statistically significant difference (*p* < 0.05) of medium effect size (standardized difference = 0.67) in cognitive performance (composite score) between Resveratrol and placebo treatments. To allow for attrition, we aimed to recruit 80 women.

### 2.3. Investigational Product and Allocation

The active and placebo capsules were of identical appearance and supplied by DSM Nutritional Products Ltd, Switzerland. The active capsule comprised 75 mg of 99% pure synthetic trans-resveratrol. The placebo comprised several inert excipients: calcium hydrogen phosphate, microcrystalline cellulose, prosolv 50 and hydrated magnesium silicate. Two hundred capsules were each dispensed in sealed white opaque containers and containers were identifiable only by code numbers. An independent investigator who held the code list allocated participants to each treatment group based on the minimisation method [30], to minimise differences between groups in age and years since ceasing menses (obtained from their health and lifestyle questionnaires) prior to the scheduled screening/baseline visit. The first participant was allocated randomly. Containers allocated to volunteers who were subsequently deemed ineligible or did not attend the screening/baseline visit were reassigned and the allocation list adjusted accordingly. Blinding will be maintained until all data analysis has been completed.

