### 2.4. Screening/Baseline Visit (Week 0)

Potentially eligible volunteers attended the 3-h screening/baseline visit after having refrained for at least an hour from medication, food or beverages other than water. Height, weight and waist circumference were measured followed by seated blood pressure (BP) readings to determine BP eligibility. Dementia status was then assessed using the Australian version of the Mini-Modified Mental State (3MS) examination. The 3MS is a widely used tool for screening suspected dementia; a score of less than 78 was considered impaired and necessitated exclusion from the study [31].

Those who met the eligibility criteria were fitted with a Transcranial Doppler (TCD) ultrasound headpiece to assess basal cerebral haemodynamics and CVR to both hypercapnic and cognitive stimuli bilaterally in the middle cerebral artery (MCA). Participant’s performances were also recorded during cognitive testing. At the conclusion of cognitive testing, participants underwent a hypercapnic assessment of CVR in the posterior cerebral artery (PCA). A physical function assessment was then carried out before a series of six paper-based questionnaires to assess mood and general wellbeing were completed to conclude the visit. Figure 1 depicts the flowchart of the participants who were enrolled in the study. It also highlights our study population size (*n* = 80, 40 per treatment group) indicating that our treatment target has been reached.

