### 2.14. Statistical Analysis

The primary outcome is the effect of resveratrol supplementation *versus* placebo on cognitive performance, determined using a composite score of all memory tests. Treatment by time effects will be determined by analysis of variance (ANOVA), or analysis of covariance (ANCOVA) in the event of interacting variables. the process of subject allocation by minimisation will have balanced age and years since cessation of menses between groups; however other baseline characteristics such as clinic BP, basal PI, BMI, 3MS score and years of education will be considered covariates if they were significantly correlated with the primary outcome.

Treatment changes in CVR to hypercapnia and/or cognitive stimuli, improvements in physical function, mood states and quality of life will be assessed using linear regressions with false rate discovery adjustments used to minimise type 1 error. In addition, to explore the potential benefits of early intervention, the magnitude of improvement following resveratrol supplementation will be compared in early (<10 years) and late (>10 years) postmenopausal women. Statistical significance for the primary outcome is set at *p* < 0.05 and false discovery rate will be applied to secondary outcomes. Statistical analyses will be performed using SPSS version 21.0 (SPSS by IBM Inc., Chicago, IL, USA).

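### Allocation preceded consent and eligibility and freed containers were reassigned by an unstated rule, yet the analysis takes balance on the two minimisation factors for granted

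*Protocol article*

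**What the plan says.** All references are to the protocol article.

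- **Before allocation (2.2).** Women returned a health and lifestyle questionnaire, and "a study investigator pre-screened volunteers via telephone to determine their potential suitability".
- **Allocation (2.3).** An independent investigator holding the code list minimised on age and years since ceasing menses, with both values "obtained from their health and lifestyle questionnaires) prior to the scheduled screening/baseline visit". On chance, the section says only: "The first participant was allocated randomly".
- **Consent (2.2).** "Written informed consent was obtained at start of the screening/baseline visit".
- **On-site eligibility (2.4).** The visit included "seated blood pressure (BP) readings to determine BP eligibility" and the 3MS, on which "a score of less than 78 was considered impaired and necessitated exclusion from the study".
- **After a failed or missed visit (2.3).** "Containers allocated to volunteers who were subsequently deemed ineligible or did not attend the screening/baseline visit were reassigned and the allocation list adjusted accordingly".
- **Analysis (2.14).** The plan states that "the process of subject allocation by minimisation will have balanced age" and years since cessation of menses. It then considers other baseline characteristics (blood pressure, pulsatility index, BMI, 3MS, education) as covariates if they correlate significantly with the primary outcome. The two minimisation factors are not on that list.

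**The concern.** Because allocation came before consent and the on-site checks, some loss of allocated women was built into the procedure. Each coded container holds one treatment, so a reassigned container brings an arm with it. Unless the recipient's arm was first worked out from her own two factors, it was set neither by chance nor by minimisation. The article does not say which happened, who did it, or whether the minimisation totals were corrected for the woman removed.

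Two things are at stake. The first is whether a reader can verify the allocation of a trial with 40 women per arm. The second is the primary analysis, which treats balance on age and years since menses as achieved and so leaves both out of the model. Factors used to allocate belong in the model in any case. To the extent that they predict the outcome, leaving them out gives up precision and makes the stated standard error too large. Years since menses also defines the early versus late postmenopausal comparison in 2.14.

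**Working it through.** **Order of events (2.2–2.4).** Questionnaire → telephone pre-screen → minimisation and container → visit → consent → blood pressure and 3MS → enrolled, or container freed and reassigned. Consent and two exclusion criteria fall after allocation.

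**Two readings of the reassignment sentence.**

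1. *Passed on:* the freed container goes to another volunteer, whose arm follows from it.
2. *Rerun:* the container returns to its arm's stock, the removed woman is taken out of the totals, and the container goes to the next woman minimised to that arm.

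The sentence fits either.

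**Size under each reading.** The article's text gives no number reassigned, and the CONSORT figure is not shown, so the loss fraction *q* is an assumption. Settings: 80 enrolled women, two balanced binary factors, minimisation with ties broken at random, totals counting enrolled women only, 1,000 simulated trials per setting. If each allocated woman is lost with probability *q* and her container goes to the next woman, the chance that any woman receives a passed-on container is *q*.

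| *q* | Share not minimised on own factors, passed on | Mean within-level arm difference (women), passed on | Same, rerun |
|---|---|---|---|
| 0 | 0% | 0.54 | 0.54 |
| 0.05 | 5% | 0.56 | 0.54 |
| 0.10 | 10% | 0.59 | 0.53 |
| 0.20 | 20% | 0.64 | 0.54 |
| 0.30 | 30% | 0.74 | 0.54 |

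**The same question in years of age.** A separate simulation of 80-woman cohorts gave these SDs of the between-arm difference in mean age: 1.78 years under simple randomisation, 0.59 under clean minimisation, and 0.64, 0.66 and 0.73 with 10%, 20% and 40% of containers passed on. The 1.78 implies an assumed age SD of 1.78 / √(1/40 + 1/40) = 1.78 / 0.2236 ≈ 8.0 years, a value the article does not give. Even at 40% loss, balance is 1.78 / 0.73 ≈ 2.4 times tighter than under simple randomisation.

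**Bound on the outcome.** A one-SD imbalance of 0.73 years is 0.73 / 8.0 ≈ 0.09 SD of age. If age correlates *r* with the composite score, the shift between arms is about 0.09 × *r* outcome SDs. That is at most 0.09 even at *r* = 1, against the design difference of 0.67.

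**Cost of leaving reassigned women out.** The planned size reproduces closely. A two-sided t-test at 0.05 with a difference of 0.67 needs 36 per arm (72 in all; the article says 74), with power 0.811 at 37 per arm and 0.841 at 40. Excluding a fraction *q* of 80 leaves 80(1 − *q*) women and widens the standard error by √(1/(1 − *q*)):

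- *q* = 0.10: 72 women, factor 1.05.
- *q* = 0.20: 64 women, factor 1.12.
- *q* = 0.30: 56 women, factor 1.20.

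At 10% or more the number falls below 74, so this analysis can only be supportive.

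**The case against.** The strongest reply is that the text describes a protected procedure. The allocator is called independent, the capsules look identical, and the containers are sealed, opaque and identifiable only by code. The on-site checks are a numerical blood pressure limit read by automated oscillometry (2.7, Table 1) and a fixed 3MS cut-off, so there is no stated route by which eligibility could depend on the arm. Minimisation with a random first allocation is a recognised form, and tie-breaking or weighting details may sit in a fuller protocol. The numbers above show little harm to balance, and 2.4 reports that all 80 women are already enrolled.

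Most of this stands, and it rules out several stronger readings that a reader might infer:

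- *That some allocations were in fact neither random nor minimised.* The sentence also fits a rerun of the minimisation, under which no woman is affected.
- *That the code-holder chose who received freed containers.* This is plausible, since nobody else is said to allocate, but the sentence is passive.
- *That the audit trail was lost.* Adjusting a list does not mean that its earlier state was discarded.
- *That the problem extends to women who withdrew during treatment.* The text covers only those found ineligible or not attending the first visit.
- *That the lack of a stated random element after the first woman is itself an error.* It is a design preference.

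The reply does not remove the point. The order of events and the re-use of containers are procedures the article itself states, not details left to another document. The analysis section then relies on the balance that this procedure was meant to deliver.

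**Conclusion.** The point holds in limited form. Allocation preceded written consent and confirmed eligibility. Containers already tied to an arm were reassigned by a rule that is not given, so the basis of those allocations cannot be verified. Section 2.14 should not rest on assumed balance or leave the two minimisation factors out of the model.

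The likely effect on balance is small: nil if minimisation was rerun, and an SD of 0.64–0.73 years rather than 0.59 for the mean-age difference if containers were passed on at 10–40% loss. These figures rest on assumed loss rates and an age SD of about 8 years. Any selection effect in the reassignment cannot be quantified from the text, and the text does not show that one occurred.

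**What to change.** For this cohort:

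1. Prespecify age and years since cessation of menses as covariates in the primary model, whatever their observed balance or correlation with the outcome. Both are already collected. The cost is two degrees of freedom: for a two-arm comparison of 80 women, 78 residual degrees of freedom become 76.
2. Keep both the original and the adjusted allocation lists.
3. Report how many women received reassigned containers in each arm, how and by whom their arm was set, and whether the minimisation totals were corrected for the women removed.
4. Add a supportive sensitivity analysis of the primary outcome without those women, stating its lower precision. This is one extra model run.

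If the design is re-used, run the minimisation at the baseline visit, after consent and confirmed eligibility, on enrolled women only. The code-holder would then have to be available during the 3-hour visit. A random element in each allocation is optional. This step comes too late for the present cohort.
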